## 12.6 Unscheduled follow-up

Unscheduled follow-up may be conducted at the request of either the study participant or the investigator. Based on the participant's condition, the investigator will perform relevant examinations including, but not limited to:

- Vital signs;
- Targeted physical examinations;
- ECOG PS assessment;
- Hemanalysis / Blood biochemistry;
- Myocardial enzymes;
- Tumor imaging evaluations.

All examination results from unscheduled visits must be documented in the eCRF.

# 13. Study Assessments

## 13.1 Efficacy assessment

The primary analysis of this study utilizes tumor assessments conducted per RECIST v1.1 criteria. All study-related decisions during trial execution will be based on local investigators' assessments of imaging results, participants' clinical status and relevant laboratory/ diagnostic findings.

## 13.2 Safety Assessment

Investigators or qualified designated personnel shall evaluate each study participant to assess potential new or worsening AEs in accordance with the trial flowchart schedule, with more frequent evaluations permitted when clinically indicated. During the study process and follow-up period, adverse events will be graded and recorded according to CTCAE 5.0. The toxicity characteristics will be determined based on several aspects: severity, causality, toxicity classification, and the measures taken regarding the trial treatment. All adverse events associated with study treatment exposure and with unknown causes should be evaluated to determine whether they may be events with potential immunological causes.

Table 2. Laboratory Safety Evaluation

| Hemanalysis | Neutrophil count (ANC), lymphocyte count (LYM), red blood cell count (RBC), hemoglobin (Hb), platelet count (PLT) |
| --- | --- |
| Blood biochemistry | Total bilirubin (TBIL), direct bilirubin (DBIL), alanine aminotransferase (ALT), aspartate aminotransferase (AST), alkaline phosphatase (AKP), total protein (TP), albumin (ALB), urea/urea nitrogen (BUN), creatinine (Cr), endogenous creatinine clearance rate (Ccr), fasting blood glucose (GLU), amylase (When blood amylase is abnormal and has clinical significance, blood lipase should also be tested), potassium (K), sodium (Na), chlorine (Cl), calcium (Ca), phosphorus (P) |
| Myocardial enzymes | Creatine Kinase (CK), Myoglobin, Creatine Kinase-MB (CK-MB), Troponin T(cTnT); |
| Coagulation function | International Normalized Ratio (INR), Activated Partial Thromboplastin Time (APTT), Prothrombin Time (PT), Fibrinogen (FIB) |

# 14. Reporting of Adverse Events

## 14.1 AEs

### 14.1.1 Definitions of AEs

An AE refers to any unfavorable medical occurrence in a clinical trial participant administered a medicinal product, which does not necessarily have a causal relationship with the treatment. An AE may be any untoward or unintended sign (including an abnormal laboratory finding), symptom, or disease temporally associated with the use of the investigational product, and must include at least the following circumstances:

(1) Pre-existing conditions: A medical condition/disease present prior to trial participation shall only be recorded as an AE if it worsens after initiation of the investigational product (including deterioration of symptoms, signs, or laboratory abnormalities);

(2) New-onset events: Any newly emergent adverse medical condition (including symptoms, signs, or newly diagnosed diseases);

(3) Clinically significant laboratory abnormalities.

Diagnostic or therapeutic procedures (invasive [e.g., surgery] or non-invasive) should not be reported as AEs. However, the underlying medical condition necessitating the procedure that meets AE criteria shall be reported (e.g., acute appendicitis occurring during the AE reporting period should be reported as an AE, while the subsequent appendectomy should be recorded as the treatment for that AE).

Any administration exceeding the protocol-specified dose by >10% constitutes an overdose. All overdose incidents must be documented in the eCRF.

### 14.1.2 AEs grade

According to the grading criteria for adverse drug events in the CTCAE 5.0 version, if an adverse event not listed in the CTCAE 5.0 table occurs, the following standards can be referred to:

Grade 1: Mild symptoms; asymptomatic or mild symptoms; clinical or diagnostic observations only; intervention not indicated;

Grade 2: Moderate symptoms; minimal, local, or noninvasive intervention indicated; limiting age-appropriate instrumental activities of daily living;

Grade 3: Severe or medically significant but not immediately life-threatening symptoms; hospitalization or prolongation of hospitalization indicated; disabling; limiting self-care ADL;

Grade 4: Life-threatening consequences; urgent intervention required;

Grade 5: Death related to AE.

Note: Distinguish between the severity and seriousness of adverse events. For example, "severe headache" may be intense in severity (e.g., Grade 3), but it does not qualify as a SAE unless it meets SAE criteria (e.g., results in hospitalization, persistent disability, or life-threatening consequences).

### 14.1.3 Assessment of AE Relationship to Investigational Product

The investigator shall determine whether there is a reasonable possibility that the investigational product caused or contributed to an AE through comprehensive evaluation. The assessment factors include:

- Temporal relationship between AE onset and investigational product administration;
- Known characteristics of the investigational product;
- Toxicological and pharmacological effects of the investigational product;
- Use of concomitant medications;
- Participant's underlying medical conditions;
- Medical history and family history;
- Dechallenge and rechallenge responses.

The causality assessment between the AE and investigational product shall be classified using the following five-category scale: Definitely related, probably related, possibly unrelated, definitely unrelated and unassessable.

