## 3.2 Secondary Endpoints

(1) Adverse drug reactions: Any noxious, unintended response to the investigational drug(s) (Irinotecan liposome + Epirubicin) at any dose, causally related to treatment (per WHO-UMC causality assessment criteria).

(2) Recurrence-Free Survival (RFS): Time from treatment initiation to histologically confirmed tumor recurrence, radiologic progression or death from any cause.

(3) Disease Control Rate (DCR): Proportion of patients achieving complete response (CR), partial response (PR) and stable disease (SD).

Note: Tumor Response Evaluation (per RECIST 1.1 criteria):

- CR: Disappearance of all target lesions; no new lesions.
- PR: ≥30% decrease in the sum of diameters of target lesions.
- SD: Neither sufficient shrinkage to qualify for PR nor sufficient increase to qualify for progressive disease (PD).
- PD: ≥20% increase in the sum of diameters of target lesions or appearance of new lesions.

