# 5. Sample Size

Both arms are expected to enroll 6-9 subjects each, with a total planned enrollment of 12-18 subjects.

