## 12.4 Safety Follow-up

The follow-up shall be conducted at 7 days (±2 days) after the last dose of study medication and includes the following:

- Adverse event assessment;
- Documentation of concomitant medications and concomitant therapies;
- Recording of subsequent anti-tumor therapies.

Collection of adverse events begins from the signing of the ICF and continues until the end of the safety follow-up period (i.e., 7 days after the last administration of the study drug or upon screening failure).If a study participant initiates new anti-tumor therapy before the end of the safety follow-up period, only AEs/SAEs suspected to be related to the study drug will be collected from the start of the new anti-tumor therapy until the end of the safety follow-up period. Any death occurring during the safety follow-up period must be reported as an SAE, regardless of whether the participant received other treatments.

After the safety follow-up period, only SAEs considered to be related to the investigational drug will be collected. For participants following the last dose of Irinotecan liposome, clinical follow-up or telephone visits will be conducted to collect information on survival status, AEs, concomitant medications, and concomitant therapies. Investigators may schedule additional visits as needed to follow up on the resolution of AEs.

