## 14.3 Collection/follow-up of AE/ SAEs

### 14.3.1 Collection of AE/SAE

The collection of AE/SAE information shall begin from the signing of the ICF and continue until the end of the safety follow-up period (defined as 30 days after the last administration of the investigational product) or Screening failure, whichever occurs first.

If a study participant initiates new anti-tumor therapy prior to the completion of the safety follow-up period, only AE/SAEs suspected to be related to the investigational product shall be collected from the start of the new anti-tumor therapy until the end of the safety follow-up period.

Any death occurring during the safety follow-up period must be reported as an SAE, irrespective of whether the participant received other treatments.

For all AEs occurring in study participants, investigators must maintain detailed documentation including: AE name, Start and end dates, Severity grade, Relationship to the investigational product, Duration, Actions taken regarding the investigational product, Outcome and Whether the event meets SAE criteria.

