### 15.5.2 Analysis Variables

Primary Endpoint: DLT

Secondary Endpoint: Adverse drug reactions, RFS, DCR,

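### The causality scale in 14.1.3 has no 'possibly related' level and is not linked to the WHO-UMC criteria that 3.2 names, so adverse drug reactions may be undercounted and late related SAEs missed

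*Protocol*

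**What the plan says.** Section 14.1.3 asks the investigator to determine "whether there is a reasonable possibility that the investigational product caused or contributed to an AE". It then makes a five-category scale mandatory: "Definitely related, probably related, possibly unrelated, definitely unrelated and unassessable". Two categories are labelled related, two unrelated, and one is neither.

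Section 3.2 defines adverse drug reactions, the first secondary endpoint, as responses "causally related to treatment (per WHO-UMC causality assessment criteria". Section 15.5.2 repeats the endpoint: "Secondary Endpoint: Adverse drug reactions, RFS, DCR". Section 14.1.3 does not refer to WHO-UMC, and section 3.2 does not refer to the five categories.

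Two collection rules also turn on relatedness. After the safety follow-up period, section 12.4 says "only SAEs considered to be related to the investigational drug will be collected". If new anti-tumour therapy starts before that period ends, section 14.3.1 says "only AE/SAEs suspected to be related to the investigational product shall be collected", and section 12.4 has a parallel sentence. Neither rule says which of the five categories it covers.

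**The concern.** The test and the scale in 14.1.3 do not fit each other. A reasonable possibility is a low threshold, and many events can be expected to meet it without being probable. Two drugs are given together, and both the underlying disease and TURBT can cause symptoms of their own. The scale goes from *probably related* straight to *possibly unrelated*, so the investigator has no accurate label for such an event.

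The endpoint also has two causality rules. Section 3.2 points to one system, while the section that governs what is recorded prescribes another.

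At stake are the count of adverse drug reactions and the completeness of late SAE collection in a phase I study whose main purpose is safety. Causality is assigned when the event is recorded. A later analysis plan can regroup the recorded categories, but it cannot restore a level that was never offered or an SAE that was never collected.

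**Working it through.** The protocol states no figure on this point, so there is none to reproduce. The check is a comparison of sections, followed by one calculation for scale.

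**Step 1: follow one event through 14.1.3.** Take an event with a reasonable but less-than-probable link to treatment. It meets the section's test. The open choices are:

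- *probably related*: overstates the link;
- *possibly unrelated*: puts an event that met the test on the side worded as unrelated;
- *unassessable*: records lack of information, when in fact a judgement was made.

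None of the three is accurate, and the protocol does not say which to use.

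**Step 2: carry the choice forward.**

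| Category chosen | Adverse drug reaction (3.2)? | Late SAE collected (12.4)? | Collected after new therapy (14.3.1)? |
| --- | --- | --- | --- |
| Probably related | Presumably yes | Presumably yes | Presumably yes |
| Possibly unrelated | Not stated | Not stated; the label suggests no | Not stated; 'suspected' could include it |
| Unassessable | Not stated | Not stated | Not stated |

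The result depends on a cut between related and unrelated that the protocol does not give.

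**Step 3: compare 3.2 with 14.1.3.** Section 3.2 names WHO-UMC. Section 14.1.3 prescribes its own list. The protocol neither sets out the WHO-UMC categories nor maps the list to them. Two systems without a link can be shown; a category-by-category conflict cannot be shown from this document.

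**Step 4: scale.** Section 5 states: "Both arms are expected to enroll 6-9 subjects each, with a total planned enrollment of 12-18 subjects". If one participant's only reaction moves to the unrelated side, the participant-level rate falls by 100/n points:

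- n = 6: 100/6 = 16.7 points
- n = 9: 100/9 = 11.1 points
- n = 12: 100/12 = 8.3 points
- n = 18: 100/18 = 5.6 points

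With exact (Clopper-Pearson) 95% intervals, the method that section 15.5.3 names for the DLT rate, 1/6 (0.4% to 64.1%) becomes 0/6 (0% to 45.9%), and 1/18 (0.1% to 27.3%) becomes 0/18 (0% to 18.5%). These figures show only how much one participant weighs. How many participants would move is unknown.

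**The case against.** The strongest reply is that no undercount has been shown. An investigator who applies the reasonable-possibility test could place a possible case in *probably related* or *unassessable*. *Possibly unrelated* does not rule out a link either; only *definitely unrelated* does. If section 3.2 governs the endpoint, WHO-UMC decides the count, and the list in 14.1.3 need not lower it. This stands: the direction of error is likely but not certain.

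The second reply is that most of the safety data are safe from the problem. From consent to the end of safety follow-up, AEs are collected whatever their cause unless new anti-tumour therapy starts (12.4, 14.3.1). Section 4.5 has SAEs, grade 3 or higher TEAEs, and TEAEs leading to discontinuation or dose change documented with no causality filter. The recorded category is kept, so tables could be rerun with *possibly unrelated* included. This largely stands for events inside the window. Such a rerun would, however, mix events that met the test with events that did not, because one label may hold both. It also cannot help with late SAEs, which are collected only if considered related. When that filter begins is itself unclear, because 12.4 ends safety follow-up 7 days after the last dose and 14.3.1 ends it at 30 days.

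The third reply is that the affected endpoint is secondary and that section 15.5.3 states no test or decision rule for it. This stands and limits the severity.

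**Conclusion.** The point holds as an internal inconsistency with a credible safety consequence. The mandatory scale lacks a level that its own section's test requires. It is not linked to the system named for the endpoint, and no cut between related and unrelated is given. Events with a reasonable but less-than-probable link may be coded as unrelated, adverse drug reactions may be undercounted, and late related SAEs may not be collected.

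A reader might infer three stronger things that the protocol does not support:

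- *That reactions will be undercounted by a given percentage.* Any such figure needs an assumed number of participants whose only link is a possible one. It also needs the assumption that none of them has another event rated definitely or probably related, since one such event keeps the participant in the count. The protocol supplies neither.
- *That the scale contradicts WHO-UMC category by category.* The WHO-UMC categories are not in the protocol. Only the absence of a mapping can be shown.
- *That the primary endpoint is affected.* Nothing in the protocol ties DLT to this scale.

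Severity is moderate: the endpoint is secondary and most events stay on record, but what is lost at recording cannot be recovered later.

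**What to change.** Use one causality system in both 3.2 and 14.1.3. This can be the WHO-UMC system already named in 3.2, with its categories written out in 14.1.3, or a single scale that includes a *possibly related* level and is cited in both places. Adding that level to 14.1.3 alone would leave the mismatch with 3.2.

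Then state which categories count as related, including how *unassessable* is handled. The protocol does not settle that last choice, so the sponsor should make it explicitly. Apply this one rule to the adverse-drug-reaction endpoint and to the collection rules in 12.4 and 14.3.1, replacing their different wordings of relatedness.

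The cost is protocol wording and one change to a CRF code list. Reported reaction rates may be higher as a result. If events have already been coded on the present list, the investigator would need to reassess those in *possibly unrelated* and *unassessable*, so the change is cheapest before data are recorded.

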## 14.2 SAE

### 14.2.1 Definitions of SAE

An SAE refers to any adverse event occurring during clinical research that meets one or more of the following criteria:

- Results in death;
- Is life-threatening (The term "life-threatening" refers to an event/reaction that places the participant at immediate risk of death at the time of occurrence (not a hypothetical risk if the condition worsened));
- Requires hospitalization or prolongs existing hospitalization;
- Causes persistent or significant disability/incapacity (Substantial disruption of the ability to perform normal life functions);
- Congenital anomaly or birth defect;
- Other medically significant events (referring to these events which, although not immediately life-threatening or causing death or hospitalization, based on reasonable medical and scientific judgment, may pose risks to the research participants, or may require intervention [such as medication or surgery] to prevent the serious consequences listed in the above definition).

### 14.2.2 Hospitalization Criteria for SAE Reporting

- In clinical studies, any adverse event leading to hospitalization (even if <24 hours) or prolonged hospitalization shall be considered an SAE. However, the following hospitalization scenarios do not require SAE reporting:
- Non-acute care facilities: Rehabilitation centers, Nursing homes;
- Routine emergency care: Emergency room visits lasting <24 hours without admission;
- Ambulatory procedures: Same-day/short-stay surgeries (outpatient/non-ambulatory settings);
- Non-medical reasons: Social/financial factors (e.g., insurance reimbursement);
- Hospitalizations or prolonged hospital stays unrelated to AE are not SAEs.

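### The short-stay surgery exemption in section 14.2.2 is too broad: read literally, it waives SAE reporting for an AE that leads to a brief surgical admission

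*Protocol*

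**What the plan says.** Section 14.2.1 lists the criteria that make an adverse event serious; meeting any one is enough. One is "Requires hospitalization or prolongs existing hospitalization", stated without exception. Another covers medically important events that "may require intervention [such as medication or surgery] to prevent the serious consequences listed in the above definition".

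Section 14.2.2 expands on the hospitalization criterion. Its general rule sets no minimum stay: "any adverse event leading to hospitalization (even if <24 hours) or prolonged hospitalization shall be considered an SAE". Exceptions follow, introduced by "However, the following hospitalization scenarios do not require SAE reporting". Three of them matter here:

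- the surgery item: "Ambulatory procedures: Same-day/short-stay surgeries (outpatient/non-ambulatory settings";
- the emergency care item, which carries a limit: "Emergency room visits lasting <24 hours without admission";
- the last item, a general one: "Hospitalizations or prolonged hospital stays unrelated to AE are not SAEs".

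Section 14.1.1 explains how a surgically treated event is recorded. The condition is the AE; in its appendicitis example, "the subsequent appendectomy should be recorded as the treatment for that AE". Section 14.3.1 requires the record of every AE to state whether it meets the SAE criteria. Section 14.5 requires an immediate report when an SAE occurs.

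**The concern.** The surgery exemption is defined by the type and length of the procedure, not by its reason. An operation done to treat an adverse event is therefore covered as readily as a planned one. If the patient is admitted for it, even briefly, the event is of the kind that the general rule takes care to include, yet the exemption releases the investigator from reporting it.

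SAEs are among the safety items named in section 4.5, and section 16 allows study activities to be suspended after one. The study's main purpose is a safety profile in 12 to 18 participants (sections 2.1 and 5). An exemption that can remove a treatment-related admission from expedited reporting deserves correction in such a study, even if it is seldom used. Two investigators could also handle the same event differently, because the setting label in the surgery item contradicts itself.

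**Working it through.** No sample size, power or event calculation bears on this point, and the protocol gives no figure to reproduce. The check is a comparison of the provisions.

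**Step 1. How the rule and the list relate.** The list is introduced as an exception to the general rule ("However, the following hospitalization scenarios do not require SAE reporting"). Within section 14.2.2 the exception governs. What matters is how far it reaches.

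**Step 2. Apply the provisions to three cases.**

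| Case | Hospitalization criterion (14.2.1, and general rule of 14.2.2) | Surgery exemption | Result |
| --- | --- | --- | --- |
| Same-day surgery for an AE, no admission | Not met | Applies, but changes nothing | No conflict |
| Short-stay admission for surgery not prompted by an AE | General rule not met; also exempt under the last item of the list | Applies, but changes nothing | No conflict |
| Short-stay admission for surgery prompted by an AE | Met, whatever the length of stay | Applies as worded | Report waived although the criterion is met |

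Only the third case is a problem.

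**Step 3. Does the wording exclude the third case?** It does not. The emergency care item is limited to visits without admission; the surgery item has no such limit and does not mention planning or cause. Its label does not settle the matter either: the item is headed as ambulatory, but its parenthesis names both outpatient and non-ambulatory settings. The second term may be a slip, but as printed it leaves the boundary open.

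**Step 4. Do other provisions catch the event?** In part. The medically significant criterion in 14.2.1 does not depend on hospitalization and names surgery as a possible intervention, so it may cover the event. Section 14.2.2 does not say that its list leaves the other criteria untouched, so this rests on the investigator's reading. The event is still recorded as an AE under 14.1.1, with its SAE status documented under 14.3.1.

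**Step 5. Size.** An undercount would need the SAE rate, the share of SAEs treated by short-stay surgery with admission, and the share of those not reported under another criterion. The protocol gives none of these. The only available arithmetic is the weight of one participant: 1/18 = 5.6% and 1/12 = 8.3% of planned enrolment. That is how far participant-level SAE incidence would move if one participant's only SAE went unreported and all enrolled participants formed the denominator. It does not show that this will happen.

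**The case against.** The strongest reply is that this is ordinary drafting: a rule, an explicit exception, and a list of overlapping examples ending in a general item. The surgery item can be read as meaning elective or outpatient procedures. The section's title and the introduction to the list confine it to hospitalization, so the other seriousness criteria remain in force. The affected event stays in the AE data and is graded and assessed for causality. If it is a treatment-emergent event of grade 3 or higher, section 4.5 has it documented in that category too. The primary endpoint is DLT, and the listed secondary safety endpoint is adverse drug reactions, not the SAE count.

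Much of this stands, and it rules out three stronger readings:

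- A reader might infer that section 14.2.2 makes the same event both an SAE and not one. It does not: the list is an exception to the rule, not a competing rule.
- A reader might argue that, because the last item already exempts stays unrelated to an AE, the surgery item can only be aimed at AE-driven surgery. The item on social and financial reasons overlaps the last item in the same way, so overlap proves nothing about intent.
- A reader might conclude that SAEs will be undercounted by a definite amount, or cite the appendicitis example as an instance. The protocol has no data on the former, and the example says nothing about admission or length of stay.

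The reply does not answer the literal reach of the item. That a narrower meaning may have been intended does not place it in the text, and the neighbouring emergency care item shows that a limit was easy to write.

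**Conclusion.** The point holds in a limited form. As worded, the surgery item waives SAE reporting for an AE-driven short-stay surgical admission, although such an event meets the hospitalization criterion in 14.2.1 and falls under the general rule in 14.2.2. This is an exemption stated too broadly, not merely a detail left open.

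The effect is confined to short-stay surgery with admission, prompted by an AE, where the investigator follows the list literally and does not report the event as medically significant or under another criterion. How often that would occur cannot be derived from the protocol. Nothing in the documents shows that the primary DLT analysis would change. The correction is worth making because it is cheap and protects safety reporting in a small phase I study.

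**What to change.** In section 14.2.2:

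1. Limit the surgery item to procedures that either involve no admission, or were planned before consent or are required by the protocol and were not prompted by an adverse event.
2. State that the list qualifies only the hospitalization criterion, and that an event meeting any other criterion in section 14.2.1 is still reported.
3. Correct the setting label so that it no longer combines outpatient with non-ambulatory.

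The same wording should go into any SAE reporting guidance given to investigators. The cost is about two sentences and a corrected label, submitted to the ethics committee as an amendment under section 17, and possibly a few more SAE reports. No treatment rule, endpoint or analysis changes.
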